#### 6.1.6 patient survey data

Study nurses contact the patients recruited for the study using the contact details entered by the practices in the personal identification database ( PiD ) . All survey data from participants are collected through a computer-assisted telephone interview (CATI) after the participant has been included in the

|                                  |                                   |                                                                                                         |                  |
|----------------------------------|-----------------------------------|---------------------------------------------------------------------------------------------------------|------------------|
| Version: V1.2                    | Last review:
February 12, 2025 | Created: [name], [name], [name], [name], [name] | Page
30 of 52 |
|                                  |                                   | Reviewed by: [name], [name]                                                    |                  |
| Release on:
February 12, 2025 | Next check:
N/A                | Released: [name]
Valid from: 04.09.2024                                             |                  |

|                   |                          |                                                                 |  |
|-------------------|--------------------------|-----------------------------------------------------------------|--|
| study
protocol | Study: „Soziales Rezept“ | Campus:
CCM                                                  |  |
|                   |                          | Scope:
Institute for General Practice and
Family Medicine |  |

study (baseline), after 3 months (3-month follow-up) and after 6 months (6-month follow-up) and entered directly into the eCRF .

### 6.1.7 documentation of the Link Worker

After the consultations with the participants, the link workers document the content of the conversation, the offers made and the duration of the consultation in the eCRF in REDCap .

This process is described in the *SocPres\_SOP Implementation of the intervention* is described in detail.

## 6.2 data with and without source data

The following data refers to source data: Personal data, contact details and long-term diagnoses of the patients (source data: patient file /practice management software) and adverse events (source data: doctor's letters for treatment in the emergency room or hospitalization, documentation in the practice management software). For all other data, the eCRF is the source document.

## 6.3 archiving and access to source data

The investigators grant study-specific access to source data and consent forms for monitoring, audits and controls by the ethics committees for up to ten years after completion of the studies.

## 6.4 instruments

*Sociodemographic data:* Based on the European Health Interview and Examination Survey (EHIS) and the Diversity Minimal Item Set ( DiMiS ), sociodemographic data (e.g. age, gender, school education, occupation, gender identity and migration background) are collected (20) . In addition , the treating general practitioners record any existing long-term diagnoses of the participants.

*Health status (WHODAS 2.0):* The WHO Disability Assessment Schedule 2.0 is a generic patient-reported outcome measure of health status. The domains of WHODAS 2.0 are based on the conceptual framework of the WHO International Classification of Functioning, Disability and Health (ICF), which has been the international standard for describing and measuring health and disability since 2001. All six ICF domains (cognition, mobility, self-care, social interaction, life activities and social participation) are covered by the WHODAS 2.0 instrument. It shows high internal consistency, high test -retest reliability and high validity compared to other instruments (21,22) . A computer-based adaptive form with 12 items is available in German.

|                                  |                                   |                                                                                                         |                  |
|----------------------------------|-----------------------------------|---------------------------------------------------------------------------------------------------------|------------------|
| Version: V1.2                    | Last review:
February 12, 2025 | Created: [name], [name], [name], [name], [name] | Page
31 of 52 |
|                                  |                                   | Reviewed by: [name], [name]                                                    |                  |
| Release on:
February 12, 2025 | Next check:
N/A                | Released: [name]
Valid from: 04.09.2024                                             |                  |

|                   |                          |                                                                 |  |
|-------------------|--------------------------|-----------------------------------------------------------------|--|
| study
protocol | Study: „Soziales Rezept“ | Campus:
CCM                                                  |  |
|                   |                          | Scope:
Institute for General Practice and
Family Medicine |  |

*Psychological well-being (WHO-5):* The World Health Organization -Five Well- Being Index (WHO-5) is a brief, self-reported measure of current psychological well-being. The scale has sufficient validity as an outcome measure in clinical trials (23) , and normative data are available for a German version (24) .

*General life satisfaction (short scale L-1 to measure general life satisfaction):* The short scale L-1 for assessing general life satisfaction consists of the item formulation established in the SOEP (25,26) . The scale contains only one item with the following wording: "How satisfied are you with your life overall at present?" The instrument has been validated in German with good reliability and normative data are available (25) .

*Loneliness (De Jong Gierveld loneliness Scale ):* The short version of the De Jong Gierveld loneliness Scale comprises 6 items and includes two subscales on emotional and social loneliness (27) . The questionnaire is valid and reliable. A validated German translation exists.

*Capability Well- being (ICECAP-A):* The ICEpop CAPability measure for Adults is a measure of well-being of the general adult population (aged 18 years and over) for use in health economic evaluation. A validated German translation exists (28) .

*Health-related quality of life (EQ-5D-5L) :* The European Quality of Life 5 Dimensions 5 Level Version is a general instrument that can be used to assess the quality of life of patients regardless of their disease. It has been extensively validated, including in the German health care context (29) .

*Subjective health status:* The health status is questioned based on the European Health Interview and Examination Survey (EHIS) as follows: How would you describe your health status in general?

*Goal-based outcome ( GBO ) :* GBOs are person-centered endpoints. Link workers and participants agree on a main goal to be achieved. Follow- ups then clarify whether this goal has been achieved or how far the person is from achieving it. The GBO is only measured in the intervention group.

*Utilization behavior (relevant sections from PECUNIA RUM or EHIS- GeDA ) :* The PECUNIA instrument for measuring resource utilization (PECUNIA RUM) measures resource utilization in all sectors of the adult population that are relevant for cost calculation from a societal perspective: health and social care, education, (criminal) justice, productivity losses and informal care (30,31) . In the present study, selected items from this measurement instrument are used that relate to the topics

|                                  |                                   |                                                                                                         |                  |
|----------------------------------|-----------------------------------|---------------------------------------------------------------------------------------------------------|------------------|
| Version: V1.2                    | Last review:
February 12, 2025 | Created: [name], [name], [name], [name], [name] | Page
32 of 52 |
|                                  |                                   | Reviewed by: [name], [name]                                                    |                  |
| Release on:
February 12, 2025 | Next check:
N/A                | Released: [name]
Valid from: 04.09.2024                                             |                  |

|                |                          |                                                              |  |
|----------------|--------------------------|--------------------------------------------------------------|--|
| study protocol | Study: „Soziales Rezept“ | Campus:
CCM                                               |  |
|                |                          | Scope:
Institute for General Practice and Family Medicine |  |

examined in the study on health and social care, as well as in the context of productivity losses, in particular hospital stays and inpatient care facilities, emergency care, outpatient health services and social services, medication, informal care, incapacity for work. If possible, the culturally adapted version of EHIS- GeDA for Germany is used.

## 7 data protection

### 7.1 data protection concept

A data protection concept was drawn up for the study and reviewed and advised by the Clinical Trial Office of the Charité Universitätsmedizin Berlin.

### 7.2 contact persons for data subject rights

The contact details of the contact persons for data subjects' rights will be communicated to the study participants in the study information.

## 8 biometrics

### 8.1 Generally

In this feasibility study, all results are interpreted exploratively.

The details of the statistical analyses (including definition of analysis populations, subgroups, sensitivity analyses, etc.) will be specified in a statistical analysis plan (SAP) before data analysis. No interim analysis is planned.

### 8.2 case number estimate

Since this is an exploratory feasibility study without confirmatory hypothesis testing, no formal sample size calculation will be performed. Based on previous experience, we assume that the analysis of a total of 215 participants (in a ratio of 2:1: 143 in the SP arm and 72 in the TAU+ arm) is sufficient to descriptively determine the feasibility and acceptability aspects of the study and to obtain further information for planning the subsequent study.

A drop-out of approximately 30% is expected, so that follow-up data for secondary clinical endpoints of 150 patients (n = 100 in the SP arm and n = 50 in the TAU+ arm) will be available after 6 months.

|                                  |                                   |                                                                                                         |                  |
|----------------------------------|-----------------------------------|---------------------------------------------------------------------------------------------------------|------------------|
| Version: V1.2                    | Last review:
February 12, 2025 | Created: [name], [name], [name], [name], [name] | Page
33 of 52 |
|                                  |                                   | Reviewed by: [name], [name]                                                    |                  |
| Release on:
February 12, 2025 | Next check:
N/A                | Released: [name]                                                                       |                  |
|                                  |                                   | Valid from: 04.09.2024                                                                                  |                  |

|                   |                          |                                                                 |  |
|-------------------|--------------------------|-----------------------------------------------------------------|--|
| study
protocol | Study: „Soziales Rezept“ | Campus:
CCM                                                  |  |
|                   |                          | Scope:
Institute for General Practice and
Family Medicine |  |

### 8.3 evaluation populations

Analyses using the Full Analysis Set (FAS) are performed according to the intention - to - treat principle with all available data (missing data are not imputed).

The per-protocol population is defined as patients who adhere to the protocol (details are defined in the SAP).

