Although non-medical health-related social problems are widespread in general practice, general practitioners can address and/or clarify only a few problems during their consultations (11) . However, in Germany, there is an extensive range of non-clinical support services and services available in the neighborhood. Nevertheless, there are no formalized links between these services and primary care (12) . Therefore, it is difficult for both general practitioners and patients to find the right contact point. Low-threshold, cooperative solutions are available here (1) .

Several possible solutions are being discussed scientifically: e.g. integrated primary care centers, social workers in primary care and social Prescribing (SP). SP was developed in the UK and has been implemented across the board in the National Health System (NHS) in recent years. Worldwide, SP programs have been introduced in several countries such as Canada, Austria and Singapore (13) . SP offers GPs a non-medical referral option that can accompany existing treatments to improve health and well-being (14) . SP is implemented through the involvement of a "link worker" to whom patients with non-medical health-related social problems are referred (= issuing a "social prescription"). Link workers are specially trained professionals or volunteers. Together with the patients, they develop an action plan and refer them to existing local services. The current evidence is based predominantly on controlled before-and-after studies; there are only a few controlled or randomized controlled studies (16) .

The available evidence indicates the need for randomized controlled trials to evaluate the effectiveness of SP - especially outside the UK. However, since there is only limited experience with establishing SP in Germany, a feasibility study is necessary to clarify various aspects of the study. Important points are the acceptance of the study, drop-out, especially in the control group, the extent of advice provided by the link worker in the German health and social system, and the feasibility of the endpoint measurements.

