### 8.4 analyses

Primary endpoints: The proportion of participants in the intervention group who attended at least one appointment with the link worker and the proportion of participants who discontinued the study before the 6-month follow-up (dropout rate) will be analyzed descriptively, with frequencies and percentages, including 95% confidence intervals per treatment group. The comparison of the dropout rate between the treatment groups will be done descriptively and using logistic regression to determine possible influencing factors.

Secondary endpoints are analyzed descriptively (frequencies/percentages, mean/standard deviation or median/interquartile depending on scale and distribution, each with corresponding 95% confidence intervals).

Comparisons between treatment groups will be performed using logistic regression (binary endpoints) or analysis of covariance (continuous endpoints adjusted for baseline , if available), taking center into account.

Safety: Adverse events are analyzed descriptively (frequencies and percentages per treatment group).

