## 16 publication guidelines

The following main publications are planned:

- Publication on the feasibility of the intervention with the primary endpoints
- Publication on clinical efficacy based on clinical endpoints
- publication on safety and adverse events
- publication on process evaluation

The principal investigator and deputy principal investigator are involved as authors in all publications. The biostatistician is involved in all publications with quantitative data. The principal investigators are involved as authors in all publications with quantitative patient data if they meet the criteria of the DFG's "Guidelines for Safeguarding Good Scientific Practice".

A publication plan is created and regularly updated, which contains the regulations on authorship . The regulations are based on the "Guidelines for Safeguarding Good Scientific Practice" of the DFG and the recommendations of the International Committee of Medical Journal Editors.

|                                  |                                   |                                                                                                         |                  |
|----------------------------------|-----------------------------------|---------------------------------------------------------------------------------------------------------|------------------|
| Version: V1.2                    | Last review:
February 12, 2025 | Created: [name], [name], [name], [name], [name] | Page
45 of 52 |
|                                  |                                   | Reviewed by: [name], [name]                                                    |                  |
| Release on:
February 12, 2025 | Next check:
N/A                | Released: [name]                                                                       |                  |
|                                  |                                   | Valid from: 04.09.2024                                                                                  |                  |

|                   |                          |                                                                 |  |
|-------------------|--------------------------|-----------------------------------------------------------------|--|

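### As written, the 6-month clinical comparison is an available-case ANCOVA on about 150 of 215 randomised patients and makes no use of 3-month scores from those lost before 6 months

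*Protocol*

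**What the plan says.** - **Missing data (section 8.3).** Analyses of the full analysis set (FAS) follow the intention-to-treat principle, with the wording "treat principle with all available data (missing data are not imputed".
- **Model (section 8.4).** Continuous endpoints are compared between arms by "analysis of covariance (continuous endpoints adjusted for baseline , if available), taking center into account". No visit term or repeated-measures model is named. Section 8.5 mentions random effects only for clustering by centre, physician or link worker.
- **Numbers (section 8.2).** "A drop-out of approximately 30% is expected" from 215 randomised, "in a ratio of 2:1: 143 in the SP arm and 72 in the TAU+ arm", so that "150 patients (n = 100 in the SP arm and n = 50 in the TAU+ arm) will be available after 6 months".
- **Outcomes.** The synopsis makes WHODAS 2.0 at 6 months the main clinical endpoint. Table 4 schedules it, WHO-5, L-1, the loneliness scale, ICECAP-A and EQ-5D-5L at baseline, 3 months and 6 months. The goal-based outcome is measured in the intervention arm only.
- **Drop-out by arm.** Section 2 lists what the feasibility study has to clarify: "Important points are the acceptance of the study, drop-out, especially in the control group". Section 4.2 also singles out loss to follow-up in the control group as something on which information is sought.
- **Use.** Section 16 plans a "Publication on clinical efficacy based on clinical endpoints". Section 8.1 calls all results exploratory and leaves details, including sensitivity analyses, to the SAP.

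**The concern.** An ANCOVA of the 6-month score takes one outcome value per patient. Without imputation, a patient with no 6-month value is left out even if a baseline and a 3-month score are on file. The 3-month score is probably the best predictor of the missing 6-month value, and the comparison does not use it.

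If patients leave between 3 and 6 months because of how they are doing at 3 months, and this pattern differs between arms, those who remain are no longer comparable. Adjusting for baseline does not repair that. The study is open and the control arm receives only a brochure, so such a difference is conceivable. At stake is the effect estimate for the main clinical endpoint, which is to be published separately and may inform the confirmatory trial.

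**Working it through.** **1. The plan's own figures reproduce.** Expected numbers with 6-month data are n × (1 − 0.30):
- 215 × 0.7 = 150.5
- 143 × 0.7 = 100.1 (SP)
- 72 × 0.7 = 50.4 (TAU+)

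The stated 150 (100 and 50) is correct. The implied drop-out is 43/143 = 30.1% in SP and 22/72 = 30.6% in TAU+, so the planning figures assume equal rates.

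**2. Patients left out at 6 months.** 215 − 150 = 65 (43 SP, 22 TAU+). The protocol does not say when they leave. If 30% to 60% of drop-outs go before month 3 (assumed), then 40% to 70% of the 65 have a 3-month score, about 26 to 45 patients.

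**3. What unequal drop-out alone does to precision.** Keep 30% overall but assume 45% in TAU+ and 22.4% in SP. This leaves 72 × 0.55 = 39.6 and 143 × 0.776 = 110.9. The standard error relative to 100 v 50 is √(1/110.9 + 1/39.6) ÷ √(1/100 + 1/50) = 0.185/0.173 = 1.07.

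**4. Bias by simulation.** The protocol gives no SD, correlations or arm-specific rates, so every input here is an assumption.
- 143:72 patients, true effect 0, outcome SD 1, 3,000 replicates per scenario, no centre effect.
- Correlations (baseline–3 m / baseline–6 m / 3 m–6 m) of 0.5/0.4/0.6, 0.6/0.5/0.7 and 0.7/0.6/0.8.
- 30% or 60% of drop-outs lost before month 3, at random within arm. Later drop-out is logistic in the 3-month score, with log-odds 0, +1 or −1 per SD.

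The ANCOVA regresses the 6-month score on arm and baseline in those observed at 6 months. The likelihood analysis regresses the 3-month score on arm and baseline (arm coefficient g) in those observed at 3 months. It then regresses the 6-month score on arm, baseline and the 3-month score (coefficients h₁ for arm and h₃ for the 3-month score) in those observed at 6 months. Its 6-month contrast is h₁ + h₃ × g. For drop-out of this pattern it serves the same purpose as a repeated-measures mixed model.

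| Drop-out TAU+ / SP | Dependence on 3-month score | ANCOVA bias (SD) |
|---|---|---|
| 30% / 30% | none, or the same in both arms | about 0 (−0.005 to 0.007) |
| 30% / 30% | TAU+ only | 0.05 to 0.08 |
| 45% / 22% | same in both arms | 0.05 to 0.06 |
| 45% / 22% | TAU+ only | 0.08 to 0.13 |
| 45% / 22% | opposite directions | 0.12 to 0.19 |

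The likelihood analysis had absolute bias of at most 0.01 SD in every scenario, and its variance was 2% to 11% lower.

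**5. Scale.** The unadjusted 95% half-width with 100 v 50 is 1.96 × √(1/100 + 1/50) = 0.34 SD. A bias of 0.05 to 0.13 SD is 15% to 38% of that; 0.19 SD is 56%.

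**The case against.** **Much of this could be left to the SAP, and all results are exploratory.** This stands in part. The protocol never says that each visit is analysed separately; that is inferred from a baseline-adjusted ANCOVA with no visit term. A missing-data sensitivity analysis belongs in the SAP and its absence here is no fault. But the protocol itself names ANCOVA and rules out imputation, and an SAP that followed both would inherit the problem.

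**A reader might infer that the protocol forecasts heavier drop-out in controls, so that bias is likely.** It does not. Sections 2 and 4.2 pose control-arm loss as a question, and section 8.2 plans equal rates. A higher control rate would still not show that drop-out depends on the 3-month score. In the scenario nearest the planning figures (30% in both arms, same mechanism) the bias is about 0.

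**A reader might infer that the 3-month data are discarded, or that the intention-to-treat label misleads.** Neither holds. The 3-month scores have their own comparison and are unused only in the 6-month one. Section 8.3 discloses in the same sentence that available data are used without imputation.

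**A reader might want the FAS redefined as patients with at least one follow-up value.** That would do harm. It would remove those lost before 3 months from the drop-out rate, and could remove patients from the link-worker attendance denominator. Both are primary endpoints.

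**The bias is small beside the uncertainty.** This is true in most scenarios: 0.05 to 0.13 SD is below one simulated standard error (0.14 to 0.17 SD). That limits the severity. It is not a reason to keep the weaker method when the data for the better one are already collected.

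**Conclusion.** The point holds for the continuous patient-reported outcomes measured at both follow-ups in both arms. As written, the main clinical contrast is an available-case analysis of about 70% of those randomised (150/215). It makes no use of 3-month scores from patients lost later, and it is unbiased only if missingness depends on nothing beyond arm, baseline and centre.

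How far the estimate would be off cannot be read from the protocol. Under the assumptions above the range is about 0 to 0.19 SD, and the top needs opposite drop-out mechanisms in the two arms. The likelihood model removes this bias when drop-out is explained by observed scores (missing at random). It cannot recover patients lost before month 3, and it does not protect against drop-out driven by unseen scores. For example, if unseen control scores were shifted by 0.2 to 0.5 SD with 30% missing in that arm only, a bias of 0.3 × 0.2 = 0.06 to 0.3 × 0.5 = 0.15 SD would remain.

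Severity is modest: the study is exploratory, and its primary endpoints are feasibility proportions that this does not touch.

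**What to change.** - **Section 8.4.** For WHODAS 2.0 and the other continuous patient-reported outcomes measured at 3 and 6 months in both arms, name one repeated-measures mixed model. The 3- and 6-month values are the outcomes; baseline, arm, visit, arm-by-visit and centre are the terms; the covariance is unstructured. Report the 6-month contrast. ANCOVA can stay as a supporting analysis.
- **Section 8.3.** Keep the FAS as all randomised participants, so that the drop-out and link-worker attendance endpoints keep their denominators. Add that the clinical comparisons use all FAS participants with at least one follow-up value, under a missing-at-random assumption. The rule against imputation can remain, because a likelihood-based model does not impute.
- **SAP.** Any analysis of departures from missing at random can be specified there.

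The cost is a few lines of text and a little more programming, with no new data. The trade-off is an explicit reliance on missing at random, which is a weaker assumption than the 6-month ANCOVA now makes implicitly.
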